## Abstract

•Wearable-based cardiac arrest detection and alerting is an emerging innovation.•The DETECT project aims to develop and validate automated cardiac arrest detection.•Key sensor inputs include photoplethysmography and accelerometer data.•Use of real patient data ensures accurate evaluation for real-world applicability.

Wearable-based cardiac arrest detection and alerting is an emerging innovation.

The DETECT project aims to develop and validate automated cardiac arrest detection.

Key sensor inputs include photoplethysmography and accelerometer data.

Use of real patient data ensures accurate evaluation for real-world applicability.

## Introduction

Survival from unwitnessed out-of-hospital cardiac arrest (OHCA) remains poor (<5%), since lifesaving interventions are often initiated too late.^1^ Wearable biosensor technology automatically detecting cardiac arrest and activating the emergency medical services (EMS) could facilitate early help for victims of unwitnessed cardiac arrest (Fig. 1)^1^, ^2^, ^3^. A recent analysis estimated an increase in OHCA survival up to 2.5 times with early recognition of cardiac arrest by biosensor technologies.^4^

**Fig. 1 f0005:**
[figure not shown]
**Schematic illustration of the proposed solution for the low survival rate of unwitnessed OHCA.** The chain of survival is often not activated, resulting in poor survival chances. A wristband with automated detection of cardiac arrest may serve as a witness. The Corsano CardioWatch 287-2 wristband is being further developed to automatically detect cardiac arrest and alert the EMS.

Several biosensors have been investigated in small studies.^5^ The most common sensor technology under investigation is photoplethysmography (PPG).^6^, ^7^, ^8^ Google recently introduced a smartwatch with ‘loss of pulse detection’ feature based on PPG and motion data, showing excellent specificity but limited sensitivity in simulation settings^9^. Other initiatives are underway.^10^, ^11^, ^12^

Among these, DETECT-1a was the first published large-scaled patient study, developing and validating an algorithm for cardiac arrest detection using wrist-derived photoplethysmography (PPG) from patients with induced cardiac arrest, achieving a 98% sensitivity.^13^ While the results were promising, it should be realized that successful future implementation warrants a highly reliable, well validated cardiac arrest detection algorithm, with excellent sensitivity and minimal false positives during daily life use to avoid unnecessary ambulance deployment. Also, practical, legal, and ethical issues surrounding implementation of this potential new technology should be addressed.

Building on the foundation established by DETECT-1a, this paper outlines the next steps of the DETECT program designed to develop, validate, and prepare for the future implementation of automated cardiac arrest detection and alarming in a daily life setting.

## Methods

### DETECT study group

Research group DETECT was founded in February 2022 with the aim to develop a technological solution for automated cardiac arrest detection and alerting. The research group consists of researchers from Radboud University Medical Center (Nijmegen, the Netherlands), Erasmus MC Cardiovascular Institute, University Medical Center Rotterdam (Rotterdam, the Netherlands), Reinier de Graaf Hospital (Delft, the Netherlands), and Corsano Health (The Hague, the Netherlands). The study protocols of all DETECT studies are assessed by the Medical Research Ethics Committee Netherlands East. Informed consent is obtained from participants/relatives before inclusion. The timeline for every study and percentage of enrolled patients is depicted in Fig. 2.

**Fig. 2 f0010:**
[figure not shown]
Percentage of enrolled patients, and enrolment timeline for the DETECT studies.

### Biosensor wristband

The DETECT studies use the CardioWatch wristband (Corsano Health, The Hague, the Netherlands; Fig. 1), a remote monitoring system that incorporates PPG sensors (green, red, infrared; sample frequency 32 Hz or 128 Hz), accelerometry sensors (sampling frequency 32 Hz), electrodes for intermittent one lead ECG recordings, and a temperature sensor. Data are transmitted wirelessly to a smartphone application and then to a health cloud for storage.

In the DETECT-1 to −3 studies, we will use the CardioWatch version 287-2 to collect PPG and accelerometer data. Concurrently, a new version of the CardioWatch (287-3) will be developed that fulfills the needs for automated cardiac arrest detection and alarming. Specifications will include a speaker, manual alarm button, cancellation button, GPS, and an LTE (Long-Term Evolution) modem for direct connection to the cloud system. The 287-3 will be able to communicate the cardiac arrest alerts to the cloud directly via 5G connection. For the cardiac arrest detection algorithm, a sample frequency of 32 Hz for both the PPG and accelerometer sensor are required, yielding a battery life of approximately 4 days.

### DETECT program

The DETECT program comprises four phases (see also Graphical Abstract), during which the wristband for automated cardiac arrest detection and alerting is developed and validated. Part 1 (DETECT-1) focuses on the development and validation of the PPG-algorithm for automated cardiac arrest detection and includes studies in patients with induced shockable arrest and cardiac arrest following withdrawal of life-sustaining treatment. Part 2 (DETECT-2) examines the value of the accelerometer in detecting a sudden falls mimicking cardiac arrest-related collapse. Part 3 (DETECT-3) shifts the focus to the home environment, investigating false-positive alarms during everyday use in a broad range of users and future target groups. Part 4 (DETECT-4) validates the newly developed CardioWatch (287-3) in a simulated setting and subsequently during at-home use in ICD patients. Below, we describe the design of the studies in detail; a complete overview of the inclusion and exclusion criteria for these studies can be found in the Supplementary Material.

### PPG-algorithm development and validation in a hospital setting [DETECT-1]

#### DETECT-1b

The DETECT-1b provides external validation of the PPG-algorithm developed in DETECT-1a. The workflow of the PPG-algorithm has previously been described.^13^ DETECT-1b is a prospective multicentre study in patients with shockable cardiac arrest, conducted in four university medical centres in the Netherlands. Adult patients (*n* = 50) in whom short-lasting cardiac arrest is induced as part of routine practice during subcutaneous implantable cardioverter defibrillator (S-ICD) implantation or ventricular tachycardia (VT) ablation are eligible for inclusion. Study participants will be equipped with a PPG wristband (CardioWatch 287-2) during the procedure. As reference standards, continuous ECG and arterial blood pressure data will be collected. All events of induced ventricular fibrillation (VF) or pulseless VT, defined as a mean arterial pressure ≤ 45 mm Hg and/or pulse pressure ≤ 15 mm Hg, are regarded as cardiac arrest events. The primary endpoint is the sensitivity for cardiac arrest detection. Secondary endpoints are the positive predictive value and false positive cardiac arrest alarms.

Based on an anticipated event rate of 60% and a 98% sensitivity observed in DETECT-1a, we determined a required sample size of approximately 50 patients is required to achieve an accurate estimate of sensitivity. Using a 95% Wilson confidence interval (CI), we obtained a range of 0.833 to 0.994 with a margin of error of approximately 8%.

#### DETECT-1c

The DETECT-1c is designed to optimize and validate the PPG-algorithm in cardiac arrest following withdrawal of life-sustaining treatment, including non-shockable arrests. It is a prospective single centre study in adult patients (*n* = ∼50) in whom life-sustaining treatment is being withdrawn in the intensive care unit (ICU). After the decision to withdraw life-sustaining treatment, verbal consent is obtained from the patient (if possible) and/or the patients’ relative(s) prior to inclusion.

Patients will wear the PPG wristband (CardioWatch 287-2) during the remaining ICU stay, including the last stages of life. Routinely recorded ECG and invasive arterial blood pressure data will be collected as reference standards. The PPG-algorithm will be used to assess the sensitivity for cardiac arrest detection and the time to detection. The previously developed PPG-algorithm for cardiac arrest detection will be optimized using iterations of ten patients each, until a sensitivity of at least 95% is reached, with a maximum number of iterations of three (i.e. 30 patients). Subsequently, the algorithm will be validated using a dataset of 20 patients. This sample size calculation is based on an anticipated sensitivity of 95%. With 20 events, sensitivity can be estimated with a margin of error of approximately 11%.

### Accelerometry algorithm development [DETECT-2]

DETECT-2 is a prospective study to develop and validate an accelerometry-based algorithm for detection of sudden falls mimicking cardiac arrest related-collapses in healthy adults (*n* = 20). Each study subject will be instructed to perform a series of fall movements on a safety mat, while wearing the CardioWatch. The falls include falls forward (from a standing position or while walking), backward, sideways, and softer falls, such as sliding off a chair or against a wall. After each fall, the participant will be instructed to lay still for at least 20 s, like in a collapse resulting from cardiac arrest. The fall movements are based on previous studies investigating videotaped sudden cardiac death.^14^, ^15^, ^16^ In addition, the participants will be instructed to perform a predefined set of activities of daily living (ADL), which will be annotated as non-fall data.

Accelerometry signals will be recorded. Video recordings from the study area will be used as a reference standard. Based on the accelerometer data, a machine learning model will be developed for the detection of the sudden falls, with a 70% training set and 30% test set. Primary endpoint is the sensitivity of the accelerometry algorithm for detection of sudden falls. Secondary endpoints include false positive fall alarms and the sensitivity to detect soft falls.

The sample size will be 20 individuls, yielding a total of 400 sudden fall events (20 events per included subject), 200 soft fall events (ten per participant), and 800 simulated non-fall events (nine different types of ADLs per included subject, performed multiple times). Targeting a sensitivity of 95% for sudden fall detection, 400 sudden fall events allow estimation of sensitivity with a margin of error of approximately 2.2% (Wilson 95% confidence interval 0.946–0.967).

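### DETECT-2 states its ±2.2% margin for all 400 sudden falls, but a 30% test set holds about 120, giving at best ±4.1%; the printed lower limit is also wrong

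*Protocol article*

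**What the plan says.** All of the relevant text is in the Protocol article, section Accelerometry algorithm development [DETECT-2].

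- Size: "The sample size will be 20 individuls, yielding a total of 400 sudden fall events (20 events per included subject").
- Model building: "a machine learning model will be developed for the detection of the sudden falls, with a 70% training set and 30% test set".
- Endpoint: "Primary endpoint is the sensitivity of the accelerometry algorithm for detection of sudden falls". The data set on which it is computed is not named.
- Precision: "Targeting a sensitivity of 95% for sudden fall detection", the section says that "400 sudden fall events allow estimation of sensitivity with a margin of error of approximately 2.2" per cent, and it prints "Wilson 95% confidence interval 0.946–0.967".

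The section does not mention cross-validation, does not say whether participants or falls are divided between training and test sets, and gives no precision for the test set.

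**The concern.** The split and the margin stand in the same section and do not fit together. Sensitivity measured on falls that trained the model is apparent performance, and a study that sets out to validate an algorithm needs performance on held-out data. The stated margin therefore describes an estimate that the planned split does not produce.

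The same programme sizes its other development studies differently. DETECT-1c uses up to 30 patients for optimisation and states its margin of about 11% for the 20 validation events only. DETECT-4a uses up to 40 participants for optimisation and states ±5% for the final subset with at least 80 simulated arrests. DETECT-2 is the exception.

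At stake is the only precision justification given for the DETECT-2 primary endpoint. A reader would expect an interval about half as wide as the one the test set can give.

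**Working it through.** **Inputs.** From the DETECT-2 section: 20 participants, 20 sudden falls each, 400 in total; anticipated sensitivity p = 0.95; two-sided 95% Wilson interval (z = 1.96); 30% test share. Assumptions: sudden falls are divided in the same 70/30 proportion as the data as a whole, and, for the clustered figures, an intraclass correlation (ICC), which the article does not give.

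**Formula.** Wilson centre = (p + z²/2n) / (1 + z²/n). Half-width = [z / (1 + z²/n)] × √[p(1 − p)/n + z²/4n²].

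**Step 1: reproduce the stated figure, n = 400.**
- Centre = (0.95 + 0.0048) / 1.0096 = 0.946.
- Half-width = (1.96 / 1.0096) × √(0.00011875 + 0.00000600) = 0.0217.
- Interval = 0.924 to 0.967.

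The 2.2% margin is therefore the figure for all 400 falls. The upper limit agrees with the article and the lower limit does not: the printed 0.946 equals the Wilson centre, and the lower limit is 0.924. The printed interval is 0.967 − 0.946 = 0.021 wide, a half-width of about 1.05 points, so it also disagrees with the 2.2% printed beside it.

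**Step 2: the test set, n = 0.30 × 400 = 120.**
- Centre = (0.95 + 0.0160) / 1.0320 = 0.936.
- Half-width = (1.96 / 1.0320) × √(0.00039583 + 0.00006669) = 0.0408.
- Interval = 0.895 to 0.977.

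The ratio to the stated margin is 0.0408 / 0.0217 = 1.9. The choice of interval matters little: the Wald half-width is 3.9 points and Clopper-Pearson gives 0.894 to 0.981.

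**Step 3: falls needed for 2.2 points in the test set.** The Wilson half-width first falls to 0.022 at n = 389. At a 30% share that is 389 / 0.30 ≈ 1,297 sudden falls in total.

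**Step 4: repeated falls within a person.** With 20 falls per person the design effect is 1 + 19 × ICC, and the effective number of falls is n divided by that. The 120-fall column applies to a split by participant (0.30 × 20 = 6 people).

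| Assumed ICC | Design effect | Half-width, 120 falls from 6 people | Half-width, 400 falls from 20 people |
|---|---|---|---|
| 0 | 1.00 | 4.1 points | 2.2 points |
| 0.02 | 1.38 | 4.9 points | 2.6 points |
| 0.05 | 1.95 | 5.9 points | 3.1 points |
| 0.10 | 2.90 | 7.4 points | 3.8 points |
| 0.20 | 4.80 | 10.0 points | 5.0 points |

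**Step 5: the sister studies on the same formula.** n = 20 gives 11.4 points (DETECT-1c states about 11%), and n = 80 gives 5.1 points (DETECT-4a states ±5%). Both margins come from the held-out data alone.

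**The case against.** The strongest reply is that the article never says that the endpoint is computed on the test set alone, so all 400 falls might be scored. That is true of the wording, but it does not rescue the margin. Scoring all 400 after training on 280 of them would mix apparent performance into the primary endpoint. Cross-validation would make 400 legitimate, but the article describes a single split.

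A second reply is that DETECT-2 is an early component study. Accelerometer data are incorporated and refined in DETECT-3, the combined model is tested prospectively in DETECT-4a, and the full system is validated in DETECT-4b. This stands, and it limits the consequence: the error is in a reported precision figure and does not undermine the programme's later validation.

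Three stronger readings are tempting, and the article does not support them.

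- *The test sensitivity will be biased upward because the same people appear in both sets.* That would follow if falls were split, but the unit of the split is not stated, and a condensed article may leave it to the full protocol.
- *The test set holds only six people.* That assumes a split by participant. It cannot hold together with the leakage reading, because under a split by fall the 120 falls could come from all 20 people. The count of about 120 falls holds either way.
- *A lower limit of 0.895 fails a requirement.* DETECT-2 sets no pass mark and no required lower limit. The aim of more than 90–95% in the Discussion is a goal for sensitivity across the programme and not a confidence limit for this study.

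A held-out 30% set is a standard design, so the split itself is not a mistake. The mistake is the margin attached to it.

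**Conclusion.** The point holds. As written, the margin of about 2.2% belongs to 400 test falls, and the planned test set has about 120. The corresponding half-width is at best 4.1 points (0.895 to 0.977), about 1.9 times the stated value. This rests on 95% sensitivity, a proportional split of sudden falls and independent falls. Dropping independence widens it: with six test participants, to about 5.9 points at an assumed ICC of 0.05 and 7.4 at 0.10.

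Separately, and without any inference about the split, the printed lower limit of 0.946 is wrong for 400 falls at 95%. It should read 0.924.

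**What to change.** Choose one of two routes and state it.

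1. **Keep the 70/30 split.** Make it by participant (14 for training, 6 for testing) and restate the precision for the test set: at best ±4.1 points (0.895 to 0.977), reported with a participant-clustered interval. Show the planning range, about ±5.9 points at an assumed ICC of 0.05 and ±7.4 at 0.10. Quoting ±4.1 alone would again be too narrow, because it treats 20 falls from one person as independent.
2. **Use leave-one-participant-out or grouped cross-validation, with all tuning inside the training folds.** Each of the 400 falls is then tested once by a model that has not seen that person. Report a participant-clustered interval and correct the printed limits to 0.924 to 0.967. The ±2.2 points then applies only if falls are independent; it is about ±3.1 at an assumed ICC of 0.05.

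The second route gives the better precision from the same participants. In either case the unit of the split should be stated, which also removes the possibility of leakage.

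The cost is analysis code and a less favourable stated margin, with no further participants or falls. Cross-validation has one drawback: it evaluates the fitting procedure and not one fixed model, and the final model would be refitted on all 20 participants.

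### DETECT-2: the printed Wilson lower limit of 0.946 is wrong; 400 falls at 95% sensitivity give 0.924–0.967, about twice the printed width

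*Protocol article*

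**What the plan says.** The section on DETECT-2 in the protocol article plans 20 healthy adults, "yielding a total of 400 sudden fall events (20 events per included subject"). The primary endpoint is the sensitivity of the accelerometry algorithm for these falls. The planning value is given as "Targeting a sensitivity of 95% for sudden fall detection", and the precision claim follows in the same sentence: "400 sudden fall events allow estimation of sensitivity with a margin of error of approximately 2.2% (Wilson 95% confidence interval 0.946–0.967").

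That sentence therefore gives three precision figures for one design: a margin of about 2.2%, a lower limit of 0.946 and an upper limit of 0.967. The same section says that the model will be built "with a 70% training set and 30% test set". The article shows no other sample-size justification for DETECT-2.

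**The concern.** The three figures cannot all be right. A range from 0.946 to 0.967 has a half-width of about one percentage point, while the margin beside it is 2.2. The range also leans the wrong way: it reaches 0.4 points below the 95% target and 1.7 points above it. A Wilson interval is pulled towards 0.5, so at 95% it should reach further below the target than above.

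The lower limit matters most here, because the programme aims for high sensitivity; the Discussion names a goal of more than 90–95%. A lower limit of 0.946 suggests that a result on target would leave almost no room for a sensitivity below 95%. If the limit is wrong, the article overstates what its primary analysis can show.

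**Working it through.** **Inputs**, all from the DETECT-2 section: sensitivity p = 0.95; n = 20 × 20 = 400 sudden falls, hence 380 detected; Wilson method; 95% confidence, two-sided, z = 1.96, z² = 3.8415.

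**Step 1. Wilson interval.**

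- Centre = (p + z²/2n) / (1 + z²/n) = (0.95 + 0.00480) / 1.00960 = 0.9457
- Half-width = z × √(p(1−p)/n + z²/4n²) / (1 + z²/n) = 1.96 × √(0.00011875 + 0.00000600) / 1.00960 = 0.0217
- Limits = 0.9457 ± 0.0217 = 0.9240 to 0.9674; width 0.0434

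**Step 2. Comparison with the printed figures.**

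| Figure | Printed | Recalculated | Reproduced? |
|---|---|---|---|
| Margin of error | about 2.2% | 2.17% (Wald: 2.14%) | yes |
| Upper limit | 0.967 | 0.9674 | yes |
| Lower limit | 0.946 | 0.9240 | no |
| Width (upper − lower) | 0.021 | 0.0434 | no, ratio about 2.1 |

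**Step 3. Consistency within the sentence.** (0.967 − 0.946)/2 = 0.0105, or 1.05%, against the printed 2.2%. The article uses the margin as the half-width elsewhere. For DETECT-1b it gives 0.833 to 0.994 with about 8%, and (0.994 − 0.833)/2 = 8.05%.

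**Step 4. Could another method or input give the printed range?** For 380 of 400:

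| Interval | Lower | Upper |
|---|---|---|
| Wilson 95%, continuity-corrected | 0.9226 | 0.9684 |
| Clopper-Pearson 95% | 0.9238 | 0.9692 |
| Jeffreys 95% | 0.9253 | 0.9682 |
| Wilson 90% | 0.9289 | 0.9651 |
| Wilson 80% | 0.9341 | 0.9622 |

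None has 0.946 as its lower limit. Nor does any other number of detected falls out of 400 give both limits. A lower limit near 0.946 needs 387 or 388 detected, with intervals 0.9452–0.9809 and 0.9483–0.9828, whose upper limits are far above 0.967. A Wilson interval close to 0.946–0.967 would need about 1,480 falls at a sensitivity of about 0.9575.

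**Step 5. Likely origin (inference).** The printed 0.946 equals the Wilson centre, 0.9457, so the range appears to run from the centre to the upper limit. The DETECT-4a section shows the same pattern. For 80 simulated arrests it prints 0.93–0.98 with ±5%. At 95% sensitivity the Wilson interval for 80 events is 0.878–0.980, with centre (0.878 + 0.980)/2 = 0.929 and half-width 5.1%. There too the margin and upper limit fit, and the centre stands where the lower limit should be.

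**The case against.** The strongest reply is that the error is narrow. The sentence leads with the margin, and the margin is right for 400 falls, as is the upper limit. A reader who plans from the 2.2% is not misled, and that figure exposes the slip. The sample size does not change. This stands: the overstatement by a factor of two applies to the printed interval, not to the margin.

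It can also be said that DETECT-2 is framed as estimation, with no null value, minimum sensitivity or go/no-go rule, so nothing in the article formally depends on 0.946, and 0.924 still lies above the lower end of the programme's goal. This is also fair. The article does not itself claim to exclude values below 94.6%; that is how a reader would take the interval. The statement that the design cannot do so holds for a result at the 95% target. With 388 of 400 detected (97%), the lower limit would be 0.948.

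Finally, the printed range contains 0.95, so its midpoint of 0.9565 is weak evidence by itself, because a Wilson interval is not centred on the observed proportion. The better argument is that at 95% the Wilson midpoint must lie below 0.95, and that of the printed range lies above it.

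None of these points yields 0.946 as a lower limit, and no other section corrects it.

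**Conclusion.** The concern holds. For 400 falls at 95% sensitivity the Wilson 95% interval is 0.924–0.967. The printed lower limit is 2.2 percentage points too favourable, and the printed interval is about half the correct width and contradicts the margin in its own sentence. The arithmetic rests only on inputs stated in the article. It is an error in a stated precision figure for a primary endpoint; the choice of 400 falls does not fail because of it.

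Even 0.924–0.967 is a best case, because it treats all 400 falls as independent and as available for estimating sensitivity. Two features of the design count against that:

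- **Split.** If the 70/30 split applies proportionally to the sudden falls, the test set holds 0.30 × 400 = 120 of them, and the interval is 0.895–0.977 (half-width 4.1%).
- **Clustering.** Each participant contributes 20 falls. The article gives no within-person correlation. For assumed values from 0.02 to 0.2, the design effect 1 + 19ρ runs from 1.38 to 4.8, and the interval for 400 falls widens from 0.919–0.970 to 0.880–0.980.

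**What to change.** Replace the lower limit 0.946 with 0.924, so that interval and margin agree, if 400 independent, evaluable falls are meant. The cost is one figure; the 2.2%, the upper limit and the number of participants stay as they are.

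Before making that edit, settle which falls will estimate sensitivity. If it is the test set only, replace the margin and both limits with values for that number of falls, and say whether they allow for repeated falls by the same person. Check the DETECT-4a interval at the same time, since it appears to contain the same slip.
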